**Aspect of HRQoL**			
DLQI	Yes	Yes	• The DLQI comprises a 10-item dermatology-specific HRQoL instrument (total score ranges from 0 to 30) [23]. • Internationally, this scale had acceptable to excellent psychometric properties, with Cronbach’s α ranges of 0.75 to 0.92 [22]. • For banding of the score, DLQI was categorized into 0–1 (no effect), 2–5 (small effect), 6–10 (moderate effect), 11–20 (very large effect), and 21–30 (extremely large effect) [22].
EQ-5D-5L	Yes	Yes	• The EQ-5D-5L measures health state utility values, 5-level assessment of mobility, self-care, usual activities, pain/discomfort, anxiety/depression, and the VAS of health state [44].
Self-rated health—WHO	Yes	Yes	• A single item is used to measure QOL based on a 5-point Likert scale of self-rated health [45].
ItchyQoL	Yes	No: translated and psychometric testing through this study	• The validity and reliability have been established on a satisfactory scale in individuals with chronic pruritus [18, 21, 25]. • The internal consistency and test-retest reliability (stability) with Cronbach’s α reliability and intraclass correlation coefficient ranges from 0.89 to 0.99 and 0.84 to 0.98, respectively [18, 25]. • For scale interpretation, ItchyQoL scores were classified as follows: 0–30 (little), 31–50 (mild), 51–80 (moderate), and 81–110 (severe) [20].
Global rating of change in HRQoL scale	Yes	Yes	• A single-item NRS of -7 (a very great deal worse) to 7 (a very great deal better) points was used to measure the degree of change in HRQoL. If participants indicated that there had been no change, they were given a score of zero [46].

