### Sample size estimation

Although we plan to include all eligible patients in this open longitudinal study, a pre-specified sample size for scale development and validation of the PRO-CP measurement tool was estimated. As such, sample size consideration for this study will be calculated based on two parameters. Firstly, we use a sample-to-item ratio (5–15 patients per question for both the EFA and CFA approach) to address a scale structure for factor analysis [8, 28, 29]. Secondly, a fair correlation coefficient statistic (>0.30) with anchor-based questions was used to establish convergent validity [34]. Regarding a power of 80% and 0.05 type I error, a minimum target of 396 patients with chronic pruritus is needed for this study cohort to account for missing responses of 20% during the cohort follow-up.

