### Statistical analysis plan

All statistical analyses will be analyzed using Stata, version 16.0 (StataCorp, College Station, Texas). The significant level was tested at *P* value <0.05 based on hypotheses of two-tailed tests. Missing values will be handled with a multiple imputation method. Descriptive statistics will be analyzed and presented as number (%), mean (SD), or median (min–max) as appropriate.

Item analysis will be assessed descriptively and summarized along with the normality of score distribution, including skewness and kurtosis tests. The Kaiser-Meyer-Olkin measure and Bartlett test of sphericity will be tested to ensure the appropriate scale factor analysis of the measurement scales. For preplanned EFA, we will employ a principle factor extraction method, with the obliquely rotated using the Promax criterion. Eigenvalues with a criterion of >1.0 will be considered as the number of factors retained. The unidimensional set or subscales will be tested using a non-parametric IRT. The item characteristics curve analysis will be visualized to describe the characteristics of individual items within the particular scale. During the follow-up period, we will perform a CFA with a maximum likelihood estimation to reaffirm the scale structure. Specific fit indices will be tested, including the comparative-fit index (>0.900), non-normed fit index or Tucker-Lewis index (<0.900), standardized root mean squared residual (<0.100), and root mean square error of approximation (<0.100).

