To assess the psychometric properties, we will test the convergent validity of the sets of PROs-CP measurement scales using Pearson’s or Spearman’s correlation coefficients as appropriate. The 95% confidence intervals (CIs) of correlation coefficient statistics will be estimated using the bootstrap resampling method. A know-group or discriminant validity will be assessed based on pruritus intensity—visual analog scale as follows: mild (0.1–2.9), moderate (3.0–6.9), severe (7.0–8.9), and very severe (9.0–10.0) [2]. Internal consistency reliability will be tested using Cronbach’s α and McDonald’s ω coefficients with 95% CIs (values of >0.7 indicate acceptable reliability). Scale reproducibility will be tested using intraclass correlation coefficients. The kappa (κ) coefficient of the agreement and area under the receiver operating characteristic curve will be used to assess the optimal cut-off severity or burden score to establish banding of measurement scales with anchor-based questions.

All interviews’ audio recordings will be transcribed verbatim. Deidentified transcript data from the in-depth interview process will be uploaded, coded, and refined by professional experts in qualitative research (RA, CP, and YR). For qualitative analysis, we will employ content analysis to summarize the interview information and assess the consistency of coding and refinement concepts that capture patient views and experiences of chronic pruritus. A thematic approach based on grounded theory techniques will be used to analyze and identify patterns or themes (subthemes) from patient perspective information [35, 36]. Furthermore, we also plan to qualitatively synthesize among subgroups with severe or very severe pruritus intensity to reflect the impacts of chronic pruritus that are most important to patients with high-burden disease activity. The saturation of concept findings from qualitative interviews will be reaffirmed using saturation tables to verify and track the concepts of how pruritus affected the patient’s life.

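### The known-group comparison across itch-VAS bands is labelled discriminant validity, and no stated empirical check compares the new or translated scales with measures of a different construct

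*Protocol article*

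**What the plan says.** The first primary objective is to establish the validity, reliability and responsiveness of the PRO set. Three translated scales (ItchyQoL, PUSH-D, TAS-20) and new scales for disease control and treatment satisfaction are to be validated.

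The Statistical analysis plan section states two empirical checks against other measures:

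- **Convergent validity.** "we will test the convergent validity of the sets of PROs-CP measurement scales", by Pearson or Spearman correlations with bootstrap 95% confidence intervals. This section gives no cut-off and names no comparator.
- **Known groups.** "A know-group or discriminant validity will be assessed based on pruritus intensity", using four VAS bands from mild to very severe. No test or pass rule is given for this check.

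The figure 0.30 appears under Sample size estimation: "a fair correlation coefficient statistic (>0.30) with anchor-based questions was used to establish convergent validity".

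Other validity evidence is described as well: expert and patient review of face and content validity, exploratory factor analysis, non-parametric item response theory and, later, confirmatory factor analysis. Table 2 lists 28 instruments (9 on pruritus, 5 on HRQoL, 14 on mental health, psychosocial and psychosomatic symptoms), including PHQ-9 and GAD-7.

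**The concern.** Known-group and discriminant validity answer different questions. A known-group check asks whether scores differ between groups that ought to differ. Discriminant validity asks whether a scale relates less strongly to other constructs than to its own. The plan names the second property and assigns it the method for the first.

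This matters because the scales target constructs meant to be distinct: itch-specific quality of life, stigma, alexithymia, disease control and treatment satisfaction. General distress is the obvious rival explanation for high scores on several of them. If distress rises with itch, a scale that measures only distress will differ across the itch-VAS bands and correlate with an itch anchor. Neither check can then tell it from a scale that measures its own construct.

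The remaining steps do not close the gap. Factor analysis and item response theory look within one scale, and a one-factor distress scale can fit well. Face and content review is judgement, not an empirical test of separation.

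**Working it through.** **1. Inputs.** From Sample size estimation: "Regarding a power of 80% and 0.05 type I error, a minimum target of 396 patients with chronic pruritus is needed", inflated "to account for missing responses of 20% during the cohort follow-up"; also "5–15 patients per question for both the EFA and CFA approach" and the 0.30 figure. From the Statistical analysis plan: "hypotheses of two-tailed tests" and the four VAS bands. Not in the documents, and therefore assumed: the true correlations of a distress-only scale with the itch anchor, the itch VAS and PHQ-9.

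**2. The plan's own figure.** To detect r = 0.30 against 0 (two-sided 0.05, 80% power):

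n = ((1.960 + 0.842) / atanh 0.30)² + 3 = (2.802 / 0.3095)² + 3 = 85, and 85 / 0.8 gives 107.

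This does not give 396. The item rule can: 22 × 15 × 1.2 = 396. The article does not state the item count; 22 is an inference from the ItchyQoL maximum of 110 at an assumed 5 points per item. The present point does not depend on how 396 arose. I use n = 396 × 0.8 = 317.

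**3. Chance that the observed r exceeds 0.30 (Fisher z, n = 317).** Standard error = 1/√314 = 0.0564. P = Φ((atanh ρ − 0.3095) / 0.0564).

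| True ρ with anchor | atanh ρ | z | P(r > 0.30) |
|---|---|---|---|
| 0.20 | 0.2027 | −1.89 | 3% |
| 0.25 | 0.2554 | −0.96 | 17% |
| 0.30 | 0.3095 | 0 | 50% |
| 0.35 | 0.3654 | 0.99 | 84% |
| 0.40 | 0.4236 | 2.02 | 98% |

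**4. Both checks together.** Simulation with 2,000 runs per setting: multivariate normal data, anchor–VAS correlation 0.5, VAS mean 5.5 and SD 2.5 (all assumed). The known-group check was counted as passed at p < 0.05, also an assumption. With the same true correlation for anchor and VAS, a distress-only scale passed both checks in 3% of runs at 0.20, 16% at 0.25, 50% at 0.30, 84% at 0.35 and 98% at 0.40. The known-group check alone was passed in 78% at 0.20 and in over 99% from 0.30. With 0.40 for the anchor and 0.20 for the VAS, the joint rate was 80%. VAS means of 4, 5.5 and 7 gave the same picture, and so did n = 396 (2%, 15%, 48%, 88% and 99% across the five values).

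**5. Adding a different-construct comparison.** Require also that the scale correlates more with the itch anchor than with PHQ-9, on point estimates. With an assumed scale–PHQ-9 correlation of 0.6 to 0.8 and itch correlations of 0.20 to 0.50, the distress-only scale passed all three checks in 0% to 1.2% of runs. An itch-specific scale (assumed 0.6 with itch, 0.4 with PHQ-9) passed in about 100%.

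**6. The same comparison as a formal test.** Meng–Rosenthal–Rubin test for dependent correlations, n = 317, correlations 0.6 and 0.4, comparators correlated 0.4:

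- mean r² = (0.36 + 0.16)/2 = 0.26
- f = 0.6/(2 × 0.74) = 0.405
- h = (1 − 0.405 × 0.26)/0.74 = 1.209
- Z = (0.6931 − 0.4236) × √(314/(2 × 0.6 × 1.209)) = 3.96
- power = Φ(3.96 − 1.96) = 98%

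With 0.6 against 0.5 and comparators correlated 0.5, the same steps give h = 1.281, Z = 2.25 and power of about 61%. A narrow separation would often stay unproven.

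**The case against.** **The text sets no acceptance rule.** A reader might infer that construct validity is accepted on r > 0.30 plus known groups alone. The article does not say so. The 0.30 figure is a planning parameter under Sample size estimation, the analysis section attaches no cut-off to the correlations, and content and structural evidence are planned as well. This objection stands. The point is therefore confined to the label and the missing comparison.

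**The pass rate rests on assumptions.** A reader might also infer that a distress-only scale would pass nearly every time. That needs a true correlation with the itch anchor of about 0.40 or more. The documents give no such value, and the joint rate runs from about 3% to 98% between 0.20 and 0.40. This stands too. Nor is passing half the time at a true correlation of exactly 0.30 a flaw of this plan; it holds for any threshold applied to a nearly unbiased estimate.

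**The article is condensed.** Named comparators and expected patterns may sit in the full protocol, and COSMIN reporting is promised. So the article cannot prove that no such analysis exists. But the sentence on discriminant validity is a positive statement that assigns a method, and condensation does not make that method fit the property.

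**The label may be a slip for discriminative validity.** That is possible. The wording would still need correcting, and no described step would separate constructs.

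**A same-construct comparator is not available for every scale.** Correct: Table 2 has no second alexithymia measure and no second stigma measure. The remedy has to differ by scale.

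**Conclusion.** The point holds in limited form. The stated method for discriminant validity is a known-group comparison, which cannot separate a scale for its own construct from one that follows itch through distress. No other stated empirical check compares the new or translated scales with different-construct measures. That conclusion rests on the text alone and needs no simulation.

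How often this would mislead is unknown. The percentages above depend on assumed correlations and on an assumed p < 0.05 rule for the known-group check. They show that the two checks can fail to screen out a distress-only scale, not that they usually would. The gain from a different-construct comparison (0% to 1.2% passing) is also conditional on assumed correlations. The documents do not support saying that a validated verdict from this study would carry little information.

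**What to change.** 1. In the Statistical analysis plan, call the itch-VAS comparison known-group validity only.
2. Assess discriminant validity with PROs already collected. Where a same- or closely related-construct measure exists, pre-specify that its correlation with the scale should exceed the correlations with PHQ-9 and GAD-7, using a dependent-correlation test. Examples are ItchyQoL with 5-D itch or DLQI, and the new disease-control and treatment-satisfaction scales with their single-item global ratings. Those single items are themselves developed in this study, so they are imperfect comparators.
3. For TAS-20 and PUSH-D, where no such measure exists, report the correlations with PHQ-9 and GAD-7 with bootstrap 95% confidence intervals, against an expectation stated beforehand.
4. Report the planned bootstrap interval beside the 0.30 benchmark, without making the lower limit a pass rule. At n = 317 such a rule would cut the pass rate at a true correlation of 0.40 from 98% to Φ(2.02 − 1.96), about 52%.

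The cost is wording and a few extra correlations, with no new data. Some scales may be reported as not distinct from distress, and a real but narrow separation may not reach significance. There is still time for the new scales: at the status date of October 30, 2024, 70 patients were enrolled and the disease-control and treatment-satisfaction scales were at item generation.

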### Ethical consideration and dissemination of the findings

#### Ethical consideration

The study protocol (version 3, March 6, 2024) was approved by the Ethics Committee of the Faculty of Medicine, Chiang Mai University (MED-2566-0299). The PROs-CP cohort will be conducted according to the Declaration of Helsinki as well as the amendments or comparable ethical standards. Written informed consent will be obtained from all patients before participating in the study. Patients will not receive financial or non-financial compensation.

All patients may withdraw their informed consent at any time during the study period. In the case of informed consent withdrawal, patients will have no effect on routine clinical management at the study site. All data collected is securely kept separate in a locked filing cabinet and will remain confidential and shared only with the authorized research team.

#### Dissemination of the findings

Any protocol amendments or justifications will be reported in the final reports for study transparency. This study protocol was followed by adapting the international, consensus-based, PRO-specific protocol guidance (the SPIRIT-PRO Extension) [37]. To disseminate the findings, we will report the study results to follow the Reporting of studies Conducted using Observational Routinely-collected health Data (RECORD) statement [38]. The reporting of the results with the psychometric properties analyses will be supplemented by the COnsensus-based Standards for the selection of health status Measurement INstruments (COSMIN) reporting guideline [39]. Moreover, the findings regarding the qualitative approach will be reported in line with the Standards for Reporting Qualitative Research (SRQR) statement [40]. We plan to disseminate the findings from this study via scientific communities and publications in peer-reviewed scientific journals.

## Discussion

Although there has been an improvement in dermatology research and the development of promising novel pharmacological therapy in recent years [41–43], the burden of chronic pruritus remains under-recognized in clinical practice. Indeed, partly or narrow set aspects of disease assessment may limit the overarching patient experiences, especially in patients with a high burden of pruritus disease and symptoms activity. Moreover, to date, little is known about the comprehensive perspectives of PRO measures on long-term outcomes among people living with chronic pruritus.

To the best of our knowledge, this is the first comprehensive set of PRO measures among patients with chronic pruritus based on a prospective longitudinal study. This study will draw evidence-based regarding the strengths of both quantitative and qualitative approaches using multistage, mixed-methods parallel designs. This study will provide detailed and nuanced information regarding the clinical utility of adopted PROs in daily dermatology practice. Taken together, we postulated that long-term PRO monitoring may help to better understand the burden of pruritus and help to optimize treatment targeted with respect to patient perspectives. However, owing to a single-center, university hospital-based cohort, this study may be limited and generalized to other settings with different healthcare systems or chronic skin disease populations should be caution.

### Cohort status

Currently, the validated non-Thai version tools (ItchyQoL, PUSH-D, and TAS-20) have been translated. Meanwhile, the measurement tools for chronic pruritus-specific disease activity control and treatment satisfaction are now under phase I—item generation of scale development. As of October 30, 2024, the PROs-CP cohort continually enrolls patients by invitation. A total of 70 eligible patients have participated in this cohort.

## Conclusions

This open cohort, prospective longitudinal study will track PROs and reflect the views and experiences of Thai people living with chronic pruritus using a mixed-methods approach. To supplement clinical outcome assessment in daily practice and help guide effective interventions, findings from the PROs-CP cohort will further leverage evidence regarding comprehensive sets of PRO measures based on the perspectives of patients with chronic pruritus. These findings also inform the utility and applicability of PRO measures and long-term outcomes among patients with chronic pruritus. Our findings will be disseminated through scientific conferences and publications in peer-reviewed journals.
